### Translators

Arabic translators are included for Arabic-speaking participants as needed. The translator is physically present during translation. The translators are trained in the management of questionnaires and the Xpsy environment for data collection. Translators assist the completion of questionnaires for Arabic-speaking participants. All translators are asked about their educational background and experience of translation, so that only translators with adequate education and experience with psychotherapy are used. All translators used in music therapy treatment are instructed in translating during induction and music listening, and they receive a self-experience of music and imagery to educate them in the special use of the voice during music and imagery with participants.

#### Statistical methods

Statistical analysis will be carried out in the statistical environment R [82] in cooperation with the statistical department in the research unit of Region Zealand and PFI Region Zealand (Production, Research and Innovation Unit). Data will be treated according to the intention-to-treat principle. Analysis of all data will take place after the conclusion of data collection. Following the initial screening of the data significance tests concerning differences between standard treatment and music therapy will be carried out in order to assess the non-inferiority of music therapy. Significance and variance for the primary outcome measure will be calculated with analysis of covariance (ANCOVA), including data from five measuring points. Secondary questionnaire outcome data will also be calculated with ANCOVA, using three data points. Correlations between trauma symptoms, attachment, dissociation and demographic parameters are investigated. A regression analysis will be applied to look for predictors of improvement of trauma symptoms (HTQ) and change of attachment style, as well as predictors for improvement connected to treatment (music therapy or standard treatment). Analysis of hormones will be split up in an ANCOVA testing variance between groups and with time (baseline to follow-up), and simple significance tests of change after single sessions (between the third and 14th session and between the interventions). Session satisfaction data will be treated with descriptive statistical methods.

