### Trial design

The research design is a randomized clinical trial with a parallel-group design including two intervention groups: music therapy (Trauma-focused Music and Imagery (TMI)) and standard psychological treatment. We use a non-inferiority framework, where we test whether or not music therapy is inferior to standard treatment. We intend to allocate 70 adult refugees diagnosed with PTSD. Repeated measures take place at baseline, post therapy and at 6 months’ follow-up. A short form of the primary outcome measure is also collected twice during the treatment period (session 5 and 10). Session evaluation from clients is collected after each session. Saliva samples are collected at baseline, post therapy and follow-up, and also pre and post sessions 4 and 14 (see the Standard Protocol Items: Recommendations for Interventional Trials (SPIRIT) flow chart; Fig. 1). All dimensions of the study protocol have been described adhering to the SPIRIT Checklist (Additional file 1). We also adhere to the revised Consolidated Standards of Reporting Trials (CONSORT) guidelines [63].

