### Dose

A significant correlation between dose and response has been found for music therapy treatment with serious mental disorders, with small effect sizes after three to ten sessions and large effects after 16 to 51 sessions [66]. A review of quantitative studies of GIM concluded, that at least ten sessions should be provided for clinical populations [67]. In our pilot study, 16 sessions provided significant changes with large effect sizes on all the outcome measures. This number of sessions also fits with the psychiatric clinic’s standard length of treatment. We chose to repeat the 16 sessions as dose for both treatment arms in the present study.

The patients participate in weekly sessions, lasting 60 min. If any cancellations occur the treatment period is prolonged until all 16 sessions have been received. Should the participant encounter any given events that would lead to further traumatizing by way of circumstances outside therapy, treatment can be prolonged to as many as 20 sessions, after consultation with the treatment team and the physician. Hence, a margin of 25% is accepted (from 12 to 20 sessions). In both music therapy and the comparator treatment a phase-oriented treatment according to Herman [68] is carried out, including a stabilizing phase, a trauma-exposure phase and a reorientation phase (if possible). The development of a safe therapeutic relationship and verbal processing are components in both psychological standard treatment and trauma-focused GIM. Thereby, the professional adaptation of music as a therapeutic medium, including the way that music influences the therapeutic relationship, is the independent variable in the trial.

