#### Phase 4. Reorientation (sessions 14–16)

In phase 4 the patients are encouraged to develop their social network and engagement in activities in their community if they are ready for it. Music and imagery can help the patient to be reminded of their dreams, and to keep them in focus as a beacon for their goals in life. Moreover, the imagery can serve as a way to rehearse new kinds of behavior in a safe environment. This phase also touches on identity and existential meaning, and the chosen music stimulates the patient to reflect upon on these cornerstones of life. The therapy course is brought to a closure, and the focus is on how the patient can go on with their life.

The described protocol is adapted to the specific needs of the patients. In case the patient cannot tolerate music at all as part of being hypersensitive to sound (which can happen due to insomnia, pain or re-traumatization), there can be sessions with only verbalization and guided imagery without music. In case the music therapist suggests that live music would be a more adequate choice than recorded music in terms of attunement to the patient, or should the patient be more able to tolerate live music, the music therapist can use their own voice and musical instruments and create music on the spot to facilitate the inner experience of the patient (as there has been examples of in the pilot study). Accordingly, patients who can tolerate short GIM (longer music and verbal interaction during the music) are offered this option.

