#### Power calculation

In order to estimate the level of power we reviewed randomized and non-randomized trials where refugees suffering from PTSD were treated with stabilization and trauma exposure strategies with cognitive and narrative elements corresponding to the standard treatment in our study, and where the Harvard Trauma Questionnaire was used to measure changes in trauma symptoms (the primary outcome in the current study). The variations in the studies were considerable, and we chose to only look at studies that had a number of sessions that were similar to the current study, and where the mean baseline value of HTQ were around 3.3, a value that we found to correspond to our population in the pilot study [18, 62, 83–86]. Non-significant differences between 0.1 and 0.5 was found in HTQ from pre to post treatment. Based on our clinical experience and data from these studies, we estimate a clinical insignificant difference of 0.3 as the maximal difference between music therapy and standard treatment to confirm the non-inferiority hypothesis. A mean standard deviation of 0.48 on post-scores of HTQ was calculated from the studies referred above.

The power calculation was based on a significance level of 0.05, power 0.08, *d* = 0.3 and *SD* = 0.48. The calculation was carried out with software from Epi-info 7 (http://wwwn.cdc.gov/epiinfo/) in cooperation with Department for Statistics, Psychiatric Research Unit, Region Zealand and PFI.

The result indicates a minimum of 64 participants (32 in each group).

Adherence to music therapy has been found to be good in psychiatric patients with a low dropout rate (11.5%) [87]. In three former randomized clinical studies on psychological treatment of refugees with large samples low dropout rates (7–10%) were demonstrated at follow-up [21, 83, 88].

We have, therefore, chosen to include a dropout rate of 10% and thus end up with *n* = 70 (35 in each group).

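### Non-inferiority is to be assessed by significance tests of a difference between arms, and the stated analysis does not compare any estimate or confidence limit with the 0.3-point HTQ margin on which the trial is sized

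*Protocol article*

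**What the plan says.** The Trial design section sets the framework: "We use a non-inferiority framework, where we test whether or not music therapy is inferior to standard treatment".

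The Statistical methods section then says how the question will be answered: "significance tests concerning differences between standard treatment and music therapy will be carried out in order to assess the non-inferiority of music therapy". The next sentence names the model: "Significance and variance for the primary outcome measure will be calculated with analysis of covariance (ANCOVA), including data from five measuring points". That section mentions no margin, shifted null hypothesis or confidence limit.

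The margin is in the Power calculation section: "we estimate a clinical insignificant difference of 0.3 as the maximal difference between music therapy and standard treatment to confirm the non-inferiority hypothesis". The same section gives an SD of 0.48 for post-treatment HTQ, a significance level of 0.05 with no sidedness, a power printed as 0.08, and a result of 64 participants (32 per group), raised to 70 for dropout.

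**The concern.** A significance test of a difference has zero difference as its null hypothesis. Non-inferiority needs the null hypothesis that music therapy is worse by 0.3 or more, and evidence that rejects it. Failing to reject zero is not such evidence. It becomes easier as the trial gets smaller or the data noisier, so poor precision favours the claim that the trial hopes to make.

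The trial is therefore sized for one test and described as analysed by another. This is not a detail left open for a statistical analysis plan, because the article itself states the means of assessing non-inferiority and names the wrong kind of test. At stake is the primary conclusion: under the described approach, a treatment that is worse by the whole margin could be reported as non-inferior with a probability that nobody has set.

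**Working it through.** **Inputs** (all from the Power calculation section unless marked)
- Margin 0.3 HTQ points; SD 0.48; 32 per arm; significance level 0.05.
- Power: printed as 0.08, read here as 0.80. Taken literally, 0.08 gives 1 participant per arm.
- True difference under the planning hypothesis: 0 (assumption; not stated).
- A higher HTQ score is worse, so a positive difference (TMI minus standard) is a disadvantage for music therapy.
- Normal approximation throughout.

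**Step 1. Reproduce the stated sample size.**
n per arm = 2 × (z₁₋α + z₁₋β)² × SD² / margin²
- One-sided 0.05: 2 × (1.645 + 0.842)² × 0.2304 / 0.09 = 31.7, so 32 per arm and 64 in total. This matches.
- One-sided 0.025 (two-sided 0.05): 2 × (1.960 + 0.842)² × 0.2304 / 0.09 = 40.2, so 41 per arm and 82 in total. This does not match.

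With a true difference of 0, the formula is the same as for a one-sided 5% test to detect a difference of 0.3. The arithmetic alone therefore cannot tell the two apart. The section's wording does, because it presents 0.3 as the limit for non-inferiority.

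**Step 2. Standard error.**
SE = 0.48 × √(2/32) = 0.12

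**Step 3. Chance that a treatment worse by the full 0.3 passes.** Here 0.3 / 0.12 = 2.5.
- Non-significance, two-sided 5%: Φ(1.96 − 2.5) − Φ(−1.96 − 2.5) = 0.295.
- Non-significance, one-sided 5%: Φ(1.645 − 2.5) = 0.196. This is the complement of the planned power of about 80%: under this reading the type II error of the difference test becomes the false non-inferiority rate.
- One-sided 95% upper limit (two-sided 90% interval) below 0.3: 0.05 by construction.

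**Step 4. The same in observed differences, at 32 per arm.**
- A disadvantage of up to 1.96 × 0.12 = 0.235 is non-significant, although its upper 95% limit is 0.235 + 0.235 = 0.47.
- Under the margin rule with a two-sided 90% interval, the observed disadvantage must be below 0.3 − 1.645 × 0.12 = 0.103.

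**Step 5. Dependence on the amount of data** (true deficit 0.3)

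| Evaluable per arm | Non-significant, two-sided 5% | Non-significant, one-sided 5% | 90% interval against 0.3 |
|---|---|---|---|
| 35 | 25.6% | 16.6% | 5% |
| 32 | 29.5% | 19.6% | 5% |
| 25 | 40.1% | 28.6% | 5% |
| 20 | 49.3% | 37.0% | 5% |

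**Step 6. Baseline adjustment.** ANCOVA multiplies the SE by √(1 − ρ²), where ρ is the baseline-outcome correlation. The article does not give ρ, so a range is assumed, at 32 per arm:
- ρ = 0.3: SE 0.114; two-sided Φ(1.96 − 2.62) = 25%; one-sided Φ(1.645 − 2.62) = 16%.
- ρ = 0.5: SE 0.104; two-sided Φ(1.96 − 2.89) = 18%; one-sided Φ(1.645 − 2.89) = 11%.
- ρ = 0.7: SE 0.086; two-sided Φ(1.96 − 3.50) = 6%; one-sided Φ(1.645 − 3.50) = 3%.

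**Step 7. Power of the margin rule at a true difference of 0** (unadjusted SE)
- Two-sided 90% interval, 32 per arm: Φ(2.5 − 1.645) = 80.4%.
- Two-sided 95% interval, 32 per arm: Φ(2.5 − 1.96) = 70.5%. With 35 per arm it is 74.4%.

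**The case against.** The strongest defence is that the design is plainly margin-based. The Power calculation section presents 0.3 as the difference that confirms non-inferiority, and a test of the hypothesis that the deficit is at least 0.3 is also, literally, a significance test concerning a difference. A full analysis plan could describe exactly that. This part stands: a reader might infer that the margin plays no role beyond sizing, or that the authors have said they will read a non-significant p-value as non-inferiority, and the article supports neither. What does not stand is that the description is adequate. The article says how non-inferiority is assessed, and its wording describes an ordinary difference test with no link to 0.3.

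The defence is also right about the numbers. Quoting only the 30% would compare a two-sided test with a one-sided 5% standard and ignore the planned baseline adjustment. The one-sided figure is 20%, and both fall with adjustment. With a high baseline-outcome correlation they come close to 5%, or below it.

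Three stronger readings are tempting, and the document does not support them.
- **Error at smaller deficits.** At a true deficit of 0.2, non-significance occurs about 62% of the time: Φ(1.96 − 0.2/0.12) = 0.615. This is not an error rate, because by the protocol's own margin a deficit of 0.2 is non-inferior.
- **Analysis set.** The article says "Data will be treated according to the intention-to-treat principle" and names no per-protocol set. Analysis sets are commonly left to the analysis plan, and the choice of set has no bearing on whether the margin is used. Nor do music-free sessions show that the TMI arm departs from protocol: the text that "there can be sessions with only verbalization and guided imagery without music" is a permitted adaptation for patients who cannot tolerate music.
- **Secondary and hormone outcomes.** These have questions and hypotheses worded as equal effectiveness, with no margins. The article sets no non-inferiority decision rule for them and labels the neuropeptide work exploratory, so a missing margin there is a matter for the analysis plan.

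**Conclusion.** The point holds as a mismatch between the stated analysis and the stated design. The method named for assessing non-inferiority is a test of difference, while the sample size and the criterion rest on a 0.3-point margin that this analysis does not use.

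If non-significance were taken as non-inferiority, the false-positive rate at the margin would be about 30% (two-sided 5%) or 20% (one-sided 5%) at 32 per arm, against 5% for the margin test. These figures assume an SD of 0.48, no baseline adjustment and a normal approximation. With an assumed correlation of 0.3 to 0.7, the two-sided figure is about 25% to 6%. Whatever its value in a given case, the rate depends on noise and numbers rather than on the margin, and it rises as evaluable data are lost.

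The conclusion does not depend on the authors intending to misread a p-value. It is enough that the described test does not address the primary hypothesis. The correction is needed before analysis.

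**What to change.** In Statistical methods, replace the difference test with a decision rule:

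- Estimate the baseline-adjusted HTQ difference, TMI minus standard treatment, at one named primary time point. The Research questions section currently names both post-treatment and 6-month follow-up.
- Conclude non-inferiority only if the upper confidence limit of that difference is below +0.3.
- State that a non-significant difference is not evidence of non-inferiority.
- State the interval level. A two-sided 90% interval matches the stated 64 evaluable participants with about 80% power. If a two-sided 95% interval is chosen, say that power at 32 per arm is about 70% on the unadjusted SD, and that 80% would need 82 evaluable participants.

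A supporting per-protocol analysis is optional and not part of the error. If one is added, the Dose section already gives a usable session range: "a margin of 25% is accepted (from 12 to 20 sessions".

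With a 90% interval, the cost is a few sentences of wording: no new data and no change in sample size. With a 95% interval, the cost is lower power or more participants.

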### Research questions

The following research questions are posed:Will music therapy (TMI) be as effective as standard treatment regarding the decrease of TSD symptoms (primary outcome) from pre to post treatment and from pre-treatment to 6 months’ follow-up?Will music therapy (TMI) be as effective as standard treatment regarding the decrease of dissociation and the improvement of attachment style and well-being (secondary outcomes) pre to post treatment and from pre-treatment to 6 months’ follow-up?Does any variable from the patient data at baseline (i.e., gender, age) specifically correlate with good outcomes of music therapy on trauma symptoms compared to standard treatment?Concerning patient satisfaction with therapy sessions, is there a difference between music therapy and verbal therapy, and is there any development in the assessment of the sessions during the therapy course?Will basic levels of salivary oxytocin, beta-endorphin and substance P be changed by the treatment, are any changes stable at follow-up, and are there differences between the two groups?Will the levels of salivary oxytocin, beta-endorphin and substance P be affected by one session, and are there a difference between the groups, and between a session at the beginning and in the end of treatment?

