## Outcome measures

The primary outcome measure is the therapist-administered Harvard Trauma Questionnaire (HTQ) [71], demonstrating an acceptable reliability in different languages, including Arabic [72, 73]. The first 16 items of part IV are used, describing to which degree the participants felt disturbed by trauma symptoms corresponding with the PTSD diagnosis in DSM-IV. The scale has three subscales: avoidance, hypervigilance and intrusion.

Eight of the HTQ questions are included in the scale PTSD-8 [74], which is administered at the beginning of sessions 5 and 10 (of 16 sessions) to monitor the effect on trauma symptoms during treatment.

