#### Blinding

There is no blinding connected to the randomization of intervention. Questionnaire data are blinded to all clinicians who are performing the treatment and data collection in the project, so that none of the clinicians or researchers have access to completed questionnaire data from their own patients or any other participant in the trial. This ensures that the clinical processes are not influenced by the outcome results data.

External psychologists are called in to assist the scoring of HTQ post treatment and follow-up, they are blinded to the treatment of the participant. Data remain concealed until the entire trial is completed.

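### The primary ANCOVA takes in two mid-therapy PTSD-8 scores alongside the three HTQ assessments and names no contrast to be tested against the 0.3 margin

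*Protocol article*

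**What the plan says.** - **Primary analysis** (Statistical methods): "Significance and variance for the primary outcome measure will be calculated with analysis of covariance (ANCOVA), including data from five measuring points". For the other questionnaires: "Secondary questionnaire outcome data will also be calculated with ANCOVA, using three data points".
- **Visits** (Trial design): "Repeated measures take place at baseline, post therapy and at 6 months’ follow-up". The same section adds: "A short form of the primary outcome measure is also collected twice during the treatment period (session 5 and 10").
- **Instruments** (Outcome measures): for the primary HTQ, "The first 16 items of part IV are used, describing to which degree the participants felt disturbed by trauma symptoms". For the short form, "Eight of the HTQ questions are included in the scale PTSD-8". That section gives the short form the role of monitoring during therapy and places it at the start of sessions 5 and 10. The Procedures list places it in sessions 6 and 11.
- **Blinded scoring** (Blinding): "External psychologists are called in to assist the scoring of HTQ post treatment and follow-up". Procedures agrees. Neither section mentions PTSD-8.
- **Question** (Research questions): whether music therapy is as effective "regarding the decrease of TSD symptoms (primary outcome) from pre to post treatment and from pre-treatment to 6 months" of follow-up. The article does not say which of the two periods decides.
- **Sizing** (Power calculation): margin 0.3 on HTQ, SD 0.48 taken from HTQ post-treatment scores, 64 participants (32 per group).

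**The concern.** The article makes a positive choice of five points for the primary analysis, and that choice does not fit its own primary outcome, research question or sample size. Two of the five points come from a half-length form, are taken while therapy is still under way, and fall outside the only blinded scoring described. Neither research-question contrast is a mid-therapy one.

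This matters more in a non-inferiority trial than in a superiority trial. Anything that shrinks the estimated arm difference makes it easier to fall inside the margin. In the indicative phases of the music therapy, session 5 closes stabilization and trauma exposure starts at session 9. It is therefore plausible, though not established, that an arm difference would be smaller at the PTSD-8 points than at the end. If those points were averaged into the tested effect, a therapy that is worse by the full margin at the end of treatment could pass too often.

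**Working it through.** **1. Where five points come from.** Baseline, post-treatment and 6 months give three HTQ scores, and the secondary questionnaires accordingly use three. The only other administrations of a form of the primary measure are the two PTSD-8 scores: 3 + 2 = 5.

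**2. The plan's own figure.** Inputs from Power calculation: margin 0.3, SD 0.48, alpha 0.05, power printed as 0.08 and read here as 0.80. Assume a true difference of zero and one time point:

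n per arm = 2 × (1.645 + 0.842)² × 0.48² / 0.3² = 31.7, so 32 per arm and 64 in all.

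The stated 64 is reproduced with a one-sided 0.05 test. A one-sided 0.025 test would give 41 per arm, or 82. The sample size is therefore that of a single post-treatment HTQ comparison.

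**3. What a time-averaged reading would do.** Assumptions that the documents do not give:
- the tested effect is the arm difference averaged over the four post-baseline points, with baseline as covariate;
- PTSD-8 is scored as an item mean on the HTQ scale, with SD 0.48 at every point;
- the correlation ρ is the same between any two points, 0.4 to 0.8;
- the deficit grows linearly over 16 sessions to 0.3 and stays there to 6 months.

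With 5 and 10 sessions completed at the PTSD-8 points, the differences are 0.3 × 5/16 = 0.094, 0.3 × 10/16 = 0.188, 0.3 and 0.3. Their mean is 0.220.

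After baseline adjustment each point has variance 0.48²(1 − ρ²), and each pair has covariance 0.48²(ρ − ρ²). So:

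SE of the four-point arm difference = 0.48 × √(2/32) × √[(1 − ρ)(0.25 + ρ)] = 0.12 × √[(1 − ρ)(0.25 + ρ)]

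P(false non-inferiority) = Φ[(0.3 − 0.220)/SE − 1.645]

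| ρ | SE | P(false non-inferiority) |
|---|---|---|
| 0.4 | 0.075 | 28% |
| 0.6 | 0.070 | 31% |
| 0.8 | 0.055 | 42% |

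If only 4 and 9 sessions are complete (PTSD-8 at the start of sessions 5 and 10), the mean is (0.075 + 0.169 + 0.3 + 0.3)/4 = 0.211 and the range is 32-49%. The conflict over session numbers thus moves the answer somewhat. Without baseline adjustment, SE = 0.12 × √[(1 + 3ρ)/4], and the 0.220 case gives 18-23%.

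**4. When the bias is absent or reversed.**
- Post-treatment contrast: the expected difference is 0.3, so P = Φ(−1.645) = 5% for any ρ.
- Full 0.3 already present at both mid-therapy points: the average is 0.3, so again 5%.
- Larger deficit in mid-therapy, for example 0.4, 0.4, 0.3, 0.3: the average is 0.35 and the adjusted rate is about 0.5-1%. Averaging is then conservative.

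**The case against.** The strongest reply is that the article says only that data from five points are included. It does not say that they are averaged, and its research question names pre-to-post and pre-to-follow-up contrasts. A repeated-measures model with arm-by-time terms, read at post-treatment, can validly use mid-therapy scores and helps retain patients who drop out. The exact contrast is a detail that a condensed article often leaves to the analysis plan. PTSD-8 also consists of HTQ items, so a common eight-item score could be formed at all five occasions.

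Most of this stands, and it rules out several stronger readings:

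- **That the plan pools the five points and so is diluted.** A reader might infer this, but no time-averaged effect is stated.
- **That the arms must look alike in mid-therapy.** More than half of the 16 sessions are done by session 10, and home music and breathing work begin in the first phase. Early differences in either direction are possible.
- **That baseline is averaged in as a fifth outcome**, which would push the mean lower still. In an ANCOVA, baseline is ordinarily the covariate, so no figure on that basis is relied on here.
- **That PTSD-8 is given unblinded.** This is a fair inference from where blinded scoring is described, but no section says who administers the form.

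What does not stand is that the point is mere silence. The article commits the primary-outcome analysis to five points. Two of them are not the defined primary measure, serve a monitoring purpose, have conflicting session numbers, and played no part in the SD or sample size.

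**Conclusion.** The point holds in a limited form. By the article's own schedule, the primary ANCOVA must include two mid-therapy PTSD-8 scores that match neither the 16-item HTQ outcome nor the single-time-point basis of the 64 participants. No contrast for the 0.3 margin is fixed. The text therefore permits a reading under which false non-inferiority is about 28-42% instead of 5%.

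That range requires both a time-averaged effect and an arm difference that builds over therapy, together with the assumed correlations of 0.4-0.8, equal SDs and a common scale. It shows the exposure left open by the wording; it is not an error rate of the plan as written.

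**What to change.** State the primary test as the between-arm difference in 16-item HTQ at post-treatment, adjusted for baseline HTQ, with its confidence bound compared with 0.3. Name the 6-month difference as key secondary. For PTSD-8, choose one of two roles:

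- a separate secondary trajectory analysis, using the eight shared items at all five occasions; or
- supporting data in a repeated-measures model with arm-by-time terms, from which only the post-treatment contrast is tested against 0.3.

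Reconcile the PTSD-8 session numbers between Trial design, Outcome measures and Procedures, and state who administers the form and whether that person knows the allocation.

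The cost is wording in the statistical methods, plus the amendment approval that the article requires for any protocol change. No new data are needed. The sample size is unchanged, because 64 was already computed for post-treatment HTQ. The article keeps outcome data concealed until the trial is complete, so the choice can be made without knowledge of the results.

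### The five-point ANCOVA for the primary non-inferiority test does not say how repeated scores from one patient are handled, and both usual readings of it have a defect that a mixed model avoids

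*Protocol article*

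**What the plan says.** The Trial design section states the aim: "We use a non-inferiority framework, where we test whether or not music therapy is inferior to standard treatment". It describes the schedule in these words: "Repeated measures take place at baseline, post therapy and at 6 months’ follow-up". It adds that a short form of the primary measure is collected twice during treatment, and Outcome measures identifies this as the PTSD-8, which uses eight of the HTQ questions. So the full 16-item HTQ is taken at three points, two of them after baseline.

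Statistical methods gives the primary analysis: "Significance and variance for the primary outcome measure will be calculated with analysis of covariance (ANCOVA), including data from five measuring points". For the other questionnaires it says: "Secondary questionnaire outcome data will also be calculated with ANCOVA, using three data points". Basic hormone levels also get an ANCOVA, between groups and over time. The same paragraph commits to intention-to-treat. It mentions no patient term, covariance structure or repeated-measures version of ANCOVA, and it names no visit for the non-inferiority test.

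The Power calculation uses a standard deviation of post-treatment HTQ scores and ends: "The result indicates a minimum of 64 participants (32 in each group".

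Three sections remove patients from the 6-month assessment. Procedures does so when additional psychotherapy is needed. Potential harms does so for patients re-traumatised by outside events who receive more treatment. Risk of bias does so for patients who leave music therapy and are offered standard treatment.

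**The concern.** The analysis named for the deciding test is not the comparison that was powered. The sample size rests on one value per patient, whereas the ANCOVA takes in five points per patient. The word ANCOVA alone does not settle how those points are combined, and the two usual readings fail in different ways.

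- **Ordinary ANCOVA on stacked rows.** Scores from one patient count as independent, and the standard error of the arm effect is too small. In a non-inferiority trial this error favours the new treatment: the interval is too narrow, and music therapy is declared non-inferior too often when it is truly worse by the full margin.
- **Classical repeated-measures ANCOVA.** Each patient's correlation is respected, but a patient missing any point is normally dropped from the whole analysis. Here the protocol creates missing 6-month values itself, in patients judged to need more or other treatment. Their observed post-treatment scores would be lost too.

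**Working it through.** **1. The plan's own sample size.** Inputs from Power calculation: margin 0.3, standard deviation 0.48, significance level 0.05, power printed as 0.08 and read here as 0.80 ("The power calculation was based on a significance level of 0.05, power 0.08"). Per arm:

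n = 2 × (z₀.₉₅ + z₀.₈₀)² × (0.48 / 0.3)² = 2 × (1.645 + 0.842)² × 2.56 ≈ 31.7, rounded up to 32.

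This matches the stated 32 per group. A one-sided 0.025 level would give 41. The stated number therefore implies a one-sided 5% test on one score per patient.

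**2. Error rate if rows are stacked as independent.** Let r be the raw correlation between any two scores of one patient, taken as equal for all pairs. The article gives no value, so 0.3, 0.5 and 0.8 are assumptions. With baseline as covariate, the remaining correlation between post-baseline rows is

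ρ = (r − r²) / (1 − r²) = r / (1 + r).

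With m post-baseline rows per patient, the variance of the arm effect is understated by the factor D = 1 + (m − 1)ρ. At a true difference equal to the margin, the one-sided 5% test declares non-inferiority with probability 1 − Φ(1.645 / √D).

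| m | r | ρ | D | 1.645/√D | False non-inferiority |
|---|---|---|---|---|---|
| 4 | 0.3 | 0.231 | 1.69 | 1.264 | 10.3% |
| 4 | 0.5 | 0.333 | 2.00 | 1.163 | 12.2% |
| 4 | 0.8 | 0.444 | 2.33 | 1.077 | 14.1% |
| 2 | 0.3 | 0.231 | 1.23 | 1.483 | 6.9% |
| 2 | 0.5 | 0.333 | 1.33 | 1.424 | 7.7% |
| 2 | 0.8 | 0.444 | 1.44 | 1.369 | 8.6% |

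Four rows means all four post-baseline points, including the two PTSD-8 scores. Two rows means HTQ at post-treatment and 6 months only.

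**3. Simulation check.** Two separate simulations used 32 patients per arm and least squares on arm, baseline and visit. At r = 0.3, 0.5 and 0.8, four rows gave 9.6%, 12.0% and 14.2% in one (6,000 replicates) and 10.4%, 11.3% and 14.4% in the other (10,000 replicates). Two rows gave 6.5%, 7.4% and 8.3% in one, and 6.7%, 7.6% and 9.0% in the other. An ANCOVA on each patient's mean stayed between about 4.5% and 5.4%.

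**4. Classical repeated-measures reading.** No inflation applies. Set the passages side by side: Statistical methods promises intention-to-treat, while Procedures, Potential harms and Risk of bias take named groups out of follow-up. A patient who has a post-treatment HTQ and is then excluded from follow-up has an incomplete row. A complete-row analysis discards that patient's post-treatment score as well. The patients lost this way are selected on need for further or different treatment, so the loss is unlikely to be random and may differ between arms. The article gives no count of such patients.

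**The case against.** The strongest reply is that the article never says rows are independent or that a patient term is left out. It calls the assessments repeated measures, describes the hormone ANCOVA as between groups and over time, and has a statistical department involved. A condensed article may leave the covariance model to a fuller document. All of this stands. A reader might infer that the trial's false non-inferiority rate simply doubles, but the article does not support that: the inflation exists only under the stacked reading, and its size depends on an assumed correlation. With the two true HTQ rows it is about 1.3-fold to 1.8-fold. A rate of twice 5% or more needs the two PTSD-8 rows as well.

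A reader might also infer that complete-row analysis takes power below the planned 80%. This cannot be shown. The number of complete patients is unknown, and baseline adjustment works the other way: at a correlation of 0.5 the standard deviation falls to 0.48 × √(1 − 0.25) = 0.416, and even an assumed 26 complete patients per arm would give about 82% (one-sided 5%, non-central t).

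Nor does the point reach the session saliva samples. The wording there, "simple significance tests of change after single sessions (between the third and 14th session and between the interventions", fits paired or change-score tests, which respect the pairing, and that part is exploratory.

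Finally, a baseline-adjusted ANCOVA at a single visit would also cure the correlation problem. That is true; a mixed model is preferred because it covers both visits and keeps patients with only one of them.

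The reply does not rescue the named method. The article makes a positive choice of an ANCOVA over five points for its deciding test, and each usual reading of that choice has a defect.

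**Conclusion.** The point holds in conditional form. The primary test is fixed as an ANCOVA over five points, two of them on another instrument, without saying how within-patient correlation is handled, in a trial sized on one post-treatment score per patient.

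- If rows are stacked: one-sided 5% false non-inferiority becomes about 10% to 14% with four post-baseline rows, or about 6.5% to 9% with two. This assumes equal correlations, raw value 0.3 to 0.8, and 32 patients per arm.
- If a classical repeated-measures ANCOVA is used: the error rate is kept, but observed post-treatment scores are discarded. This conflicts with intention-to-treat, risks selection bias, and lowers power relative to using all patients, by an amount the article does not fix.

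This should be changed before the data are analysed. It does not show that the trial will reach a wrong conclusion.

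**What to change.** In Statistical methods, replace the five-point ANCOVA with a mixed model for repeated measures on HTQ at post-treatment and 6 months. Include baseline HTQ by visit, arm by visit and an unstructured within-patient covariance, with all randomised patients who have any post-baseline HTQ, analysed in their allocated arm. Take the non-inferiority contrast at post-treatment, the score on which the trial was sized, and compare it with the margin set by this sentence: "we estimate a clinical insignificant difference of 0.3 as the maximal difference between music therapy and standard treatment to confirm the non-inferiority hypothesis". Use the same form of model for the three-point secondary questionnaires and the basic saliva levels. PTSD-8 stays outside the primary model.

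The cost is a change of wording, reported through the article's amendment route, and a standard mixed-model fit in R. No extra patients or data are needed. Analysis starts only after data collection ends, so the method can be settled before results are seen. The downside is that intervals will be somewhat wider than a pooled ANCOVA would print. The model also does not fully remove bias if the missing 6-month values depend on unobserved outcomes.
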